**Table S8. Number Need to Treat for PCC Intervention on Retention in care at 15 months and Missing Next Visit by >30 days**

|                             | Retention in Care at 15m             |           | Missed Visits by 30 days             |           |                                      |           |
|-----------------------------|--------------------------------------|-----------|--------------------------------------|-----------|--------------------------------------|-----------|
|                             |                                      |           | Control vs. Intervention <6m         |           | Control vs. Intervention >6m         |           |
|                             | Adjusted Risk Difference
(95% CI) | NNT       | Adjusted Risk
Difference (95% CI) | NNT       | Adjusted Risk
Difference (95% CI) | NNT       |
| Overall              | 5.9
(0.6 – 11.2)    | 17 | -2.1
(-2.50 – -1.7) | 48 | -4.2
(-4.8 – -3.7)  | 24 |
| Baseline Care Status |                                      |           |                                      |           |                                      |           |
| New ART                     | 12.7
(1.4 – 23.9)                 | 8         | -1.3
(-2.8 – 0.3)                 | 80        | -5.0
(-7.4 – -2.7)                | 20        |
| In Care                     | 4.1
(0.2 – 8.0)                   | 25        | -2.5
(-3.0 – -2.1)                | 40        | -4.6
(-5.2 – -3.9)                | 22        |
| Returner                    | 5.0
(0.0 – 10.1)                  | 20        | -0.6
(-1.6 – 0.4)                 | 163       | -2.1
(-3.6 – -0.6)                | 48        |
| Sex                  |                                      |           |                                      |           |                                      |           |
| Female                      | 6.6
(0.8 – 12.4)                  | 15        | -2.9
(-3.4 – -2.4)                | 35        | -5.6
(-6.3 – -4.9)                | 18        |
| Male                        | 3.7
(0.0 – 7.4)                   | 27        | -0.7
(-1.3 – -0.1)                | 146       | -1.9
(-2.9 – -1.0)                | 51        |

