### **Sample size estimation**

Assuming that 75% of individuals are virally suppressed at baseline and very conservative intraclass correlation between facilities of 0.2, we estimated that we would be able to detect a 10.7% difference between intervention and control arms with 80% power and at  $p<0.05$  if we used approximately 60 patients at each clinic at each of the 16 facilities in waves 1 and 4, for a total maximum of approximately 960 (480 in sequence 1 & 480 sequence 4) viral loads. At each facility, we sought to balance recruitment among new ART starters, individuals who were more than 30 days late (lost or late), and individuals who were in care). The reason for using a sub-cohort is that in we sought to evaluate effects in a “real world” delivery setting, but in these setting outcome ascertainment under routine conditions can be a challenge. By identifying a sub-cohort who are representative of all, but in whom additional data collection at baseline about contact information will allow more intensive outcome ascertainment at the end of the trial to ensure outcome ascertainment.

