#### Study Population:

TEC patients are drawn from patients who were adults over 18 years of age at time of recruitment, on or had been on treatment, with at least one clinical visit between 17th August 2019 and 17th November 2021 (which we used to define the study population) in study facilities. TEC patients were included both patients in care (who were recruited in the waiting room through systematic sampling of every kth patient where k depended on the facility size) as well as patients who had been in care but were lost to follow up (at least 30 days late for a visit) who were approached through the phone or contact through tracing in the field. The patients were drawn from facilities in waves 2, 3 and 4 during both control and intervention periods (Figure)

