## 5.2 - Missed Next visit

**Outcome:** This secondary outcome for retention will be whether an individual misses their next visit by more than 30 days. We will use EHR data (i.e., SmartCare) that includes sociodemographic, clinical, visit history, and pharmacy data to determine this outcome. These complement 15th month assessments because are able to consider shorter term effects of the intervention rather than a single endpoint at 15 months which reflect the cumulative effects over all observation time until that time point.

**Population:** The population for this outcome will include all individuals ( $\geq 18$  years old) who made a visit to one of our study clinics during the 6 months prior to our study and period through to the end of the 24-month study period. This analysis will include individuals from facilities in all waves.

|        | Period 0                                                   | Period 1                                                        | Period 2                                                        | Period 3                                                        | Period 4                                                        | Totals per wave |
|--------|------------------------------------------------------------|-----------------------------------------------------------------|-----------------------------------------------------------------|-----------------------------------------------------------------|-----------------------------------------------------------------|-----------------|
| Wave 1 | Control
All Visits made during Period
~60,000 | Intervention
All Visits made during Period
~60,000 | Intervention
All Visits made during Period
~60,000 | Intervention
All Visits made during Period
~60,000 | Intervention
All Visits made during Period
~60,000 | ~300,000 visits |
| Wave 2 | Control
All Visits made during Period
~30,000 | Control
All Visits made during Period
~30,000      | Intervention
All Visits made during Period
~30,000 | Intervention
All Visits made during Period
~30,000 | Intervention
All Visits made during Period
~30,000 | ~150,000 visits |

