Analysis: This analysis will include data from all studies leveraging the full stepped-wedge design. The 6-month period prior to study start will be included as a Period 0 when all facilities are control. We will use mixed effects logistic regression, accounting for clustering at both the individual- and the facility-level using random effects. The main exposure will be exposure to the PCC intervention and will be assigned at the visit level. As some individuals may be seen more than once during the study period and cross-over from control to intervention, each visit will be categorized as control or intervention based on when it occurred (e.g., an individual may have one visit assigned as control and a later visit categorized as intervention). Due to a potential lag in intervention effect, we will code intervention periods as control, early intervention ( $\leq 6$  months), and late intervention ( $> 6$  months) (Hughes et al., 2015; Kenny et al., 2021). To account for potential imbalances due to cluster randomization at baseline and also increase precision, we will adjust for individuals' care status at enrollment (in care, new ART, LTFU), sex, age, time in care, baseline clinic-level retention (i.e., percent of visits where patient was more than 30 days late to their next appointment assessed in the 6 months prior to study start), and randomization strata (initial cluster randomization stratified by facility size and viral load coverage based on programmatic data). Facility will be included as a random effect. We will consider including the following potential confounders due to imbalance in randomization: WHO severity groups, marital status, and education. We will use standard model diagnostic procedures and consider alternate specifications as needed if we face challenges with standard statistical issues such as model convergence or overfitting. We will use marginal estimation commands to report absolute and relative risk differences under treatment versus control conditions.

In addition to the overall analysis, we will perform stratified analyses to assess changes specifically across:

- Care Status at time of visit (in care, new ART, LTFU)
- Sex
- Age (<25, 25-44, >45)
- Advanced HIV Disease at enrollment in care (WHO Stage 3 or 4, CD4<200) – Dependent on adequate coverage of CD4 measurements
- Clinic Size and Type

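### SAP 5.2 stratifies missed visits by care status at each visit, which after crossover is largely an earlier outcome, so the LTFU and in-care effects may be biased in an unknown direction

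*Combined protocol and SAP*

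**What the plan says.** The outcome in SAP 5.2 is "whether an individual misses their next visit by more than 30 days". Exposure is assigned visit by visit: "each visit will be categorized as control or intervention based on when it occurred". It is then split by time since crossover ("we will code intervention periods as control, early intervention" and late, the cut being six months). People contribute repeated visits, with random effects for individual and facility.

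Section 5.2 uses care status in two ways. The model adjusts for "care status at enrollment (in care, new ART, LTFU", but the stratified analyses use "Care Status at time of visit (in care, new ART, LTFU".

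Section 5.2 does not define LTFU. SAP 4.0 (TEC study population) describes it as "lost to follow up (at least 30 days late for a visit", and SAP 3.0 (sample size) speaks of "individuals who were more than 30 days late (lost or late". For the primary outcome, SAP 3.0 takes the corresponding subgroup at entry to the cohort. The sensitivity analyses in 5.2 vary the lateness threshold and the lag to full effect, not the definition of the subgroup.

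Tables S8 and S13 head the reported missed-visit rows "Baseline Care Status", which is not what 5.2 specifies.

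**The concern.** Randomisation makes control and intervention visits comparable, allowing for period, within strata formed before exposure. It does not do so within strata that exposure can alter. Once a facility has crossed over, whether a returning patient counts as LTFU or in care depends on the last appointment, which may itself have been kept or missed under the intervention. The LTFU visits in the two conditions can then come from different kinds of patient, and so can the in-care visits.

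At stake is the reading of who benefits. At more than six months, Table S8 shows -2.1 points in returners and -4.6 in patients in care. If the 5.2 rule produced those rows, that contrast is not a randomised comparison within groups defined beforehand. If baseline status was used instead, the analysis departed from the SAP without saying so.

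**Working it through.** **Status and outcome side by side.** The outcome at visit k is lateness of more than 30 days for visit k+1. LTFU status at visit k+1, on the SAP's definitions elsewhere, is about 30 days' lateness for that same visit. So status at k+1 is largely the outcome at k. If visit k fell after crossover, that status is post-exposure. Two cases escape: a person's first visit after crossover, whose preceding visit was made under control, and new-ART status, which does not come from a missed visit.

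**The plan's own figures.** SAP 5.2 gives no power calculation, only visit counts, and these add up: 5 × 180,000 = 900,000, and 300,000 + 150,000 + 150,000 + 300,000 = 900,000. In Table S13, 130,035/587,479 = 22.1% of control visits were followed by a missed visit, as printed. The care-status Ns also sum correctly: 54,391 + 805,353 + 149,608 = 1,009,352.

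**Direction of bias, by simulation.** None of these inputs is in the documents. There are 2,000,000 people with four visits, under control or under intervention throughout. Baseline logit is -1.4 (about 20% missed), the intervention log-odds effect is -0.3, and a previous miss adds 0.5. Frailty is a normal person-level intercept. *At visit* is the risk difference by status at the last visit. *Causal* is the intervention's effect on the next visit among control-condition members of the same stratum. Values are percentage points.

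| Scenario | LTFU at visit | LTFU causal | In care at visit | In care causal |
|---|---|---|---|---|
| A. No shared frailty | -5.76 | -5.76 | -4.34 | -4.34 |
| B. Frailty SD 0.5 | -5.83 | -6.10 | -4.04 | -4.23 |
| C. Frailty SD 1 | -5.13 | -6.23 | -3.32 | -3.89 |
| D. SD 1, effect -0.6 in a random half, none in the rest | -3.96 | -6.07 | -3.31 | -3.59 |
| E. SD 1, intervention brings back low-frailty lapsers | -10.03 | -6.06 | -2.97 | -3.62 |
| E2. SD 1, intervention brings back high-frailty lapsers | +4.18 | -6.07 | -1.35 | -3.62 |
| F. As D, and responder lapsers return more often | -3.07 | -2.96 | -2.34 | -2.99 |

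In E and E2, lapsed patients return with probability 0.5 under control; under intervention this is 0.95 for frailty below 0.5 (E) or above 0.5 (E2). In F, responders return with probability 0.4 under control and 0.95 under intervention, and the others with 0.8 in both. In F the causal effect is -2.96 in control-condition LTFU members but -5.76 in intervention-condition members, so the strata hold different people.

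**What the reported tables show.** N-weighted averages of the stratum effects, compared with the overall effect:

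- Table S13, late, by care status: (54,391 × -4.7 + 805,353 × -3.4 + 149,608 × -2.0)/1,009,352 = -3.26, against -3.7 overall. By sex the average is -3.74 and by age -3.72.
- Table S13, early: -1.75 by care status, against -2.0 overall; -2.01 by sex and by age.
- Table S8, using S13 Ns as assumed weights because S8 prints none: -4.25 against -4.2 late, and -2.15 against -2.1 early. The in-care late effect (-4.6) is further from zero than the overall effect (-4.2).

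S13 would fit some attenuation; S8 would not.

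**Returner share of visits, from S13.** Early: 8,526/0.296 = 28,804, and 28,804/178,523 = 16.1%. Late: 14,660/0.290 = 50,552, and 50,552/243,350 = 20.8%. Control: 149,608 - 28,804 - 50,552 = 70,252, and 70,252/587,479 = 12.0%. Stratum make-up changes with exposure category, but calendar time and COVID-19 change with it too.

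**The case against.** A reader might infer that the subgroup effects are biased toward zero, or that the returner versus in-care contrast in Table S8 is an artefact. The documents support neither.

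- **Direction.** Attenuation is the simplest case, under shared frailty and a uniform effect. Without shared frailty there is no bias. If the intervention changes who comes back, the LTFU estimate can be exaggerated or reversed. The documents give no frailty or return parameters.
- **Size.** Scenario C retains 5.13/6.23 = 0.82 of the LTFU effect. Undoing that turns -2.1 into about -2.6. Scenario D retains 3.96/6.07 = 0.65, giving about -3.2. Both remain short of -4.6, and the in-care figure would grow as well.
- **Timing.** An artefact of post-exposure status should build up with exposure. In Table S8 the returner effect is weakest relative to in care early (-0.6/-2.5 = 0.24) and less so late (-2.1/-4.6 = 0.46).
- **Returner share.** If the intervention only prevented missed visits, the share should fall. It rises, which points to calendar time or to more lapsed patients returning; in the second case the direction of bias is open.
- **Provenance.** The rows are labelled baseline. If that is correct, they do not come from the 5.2 rule at all. Nor do these documents state that returning patients gain less.

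All of this stands against a firm direction or size. It does not rescue the planned subgroup. Status at visit is a natural descriptor when exposure is assigned per visit, but it is not a pre-exposure one. The individual random effect and the enrollment-status covariate may absorb some frailty. They are not a dependable cure, because stratifying on a lagged outcome makes stratum membership correlate with the random intercept.

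**Conclusion.** The LTFU and in-care subgroup effects specified in SAP 5.2 condition on an earlier value of the outcome at repeat visits after crossover. They are not protected by randomisation and may be biased. Direction and size cannot be determined from the documents: the simulated LTFU bias was nil, toward zero, away from zero or sign-reversing, depending on assumed inputs, and the in-care bias was nil or toward zero in the scenarios tried.

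The conclusion assumes that LTFU in 5.2 carries the roughly 30-day meaning given elsewhere in the SAP. A different threshold would weaken the identity with the outcome but would leave status dependent on earlier lateness.

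The scope is limited to one subgroup variable for a secondary outcome. The overall missed-visit effect does not use it, and new-ART status does not arise from a missed visit. It is worth correcting because the subgroup bears on who benefits, no planned sensitivity analysis would expose the problem, and the SAP and the table labels disagree.

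**What to change.** In SAP 5.2, make the main care-status subgroup the status at the individual's first visit in the analysis window (Period 0, or the first later visit), carried unchanged to all later visits. Define enrollment status explicitly for this EHR cohort so that subgroup and model covariate agree. Where Period 0 visits are left out of the model, as the Table S13 footnote describes for the main manuscript, the EHR can still supply Period 0 status for Group 1.

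Status at the last visit before the facility's crossover, carried forward, is an alternative. It needs a rule for control visits made before that visit, so that they are not classified by something that happened afterwards.

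Add a check restricted to individuals first seen before their facility's crossover, because status at entry is still post-rollout for later entrants. Keep status at visit only as an exploratory, post-randomisation description. State which definition produced the rows in Tables S8 and S13, and correct either the labels or the SAP wording.

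The cost is small: SAP text, one rerun stratified table and one restricted check. The trade-off is that a fixed status becomes less current at later visits; someone who entered as new ART keeps that label.

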## 1.0 BACKGROUND AND INTRODUCTION

The scale-up of human immunodeficiency virus (HIV) treatment services has expanded rapidly in Zambia, facilitated by the evolution of the HIV response from centralized services to decentralized care and now towards differentiated service delivery models. Nevertheless, optimal effectiveness remains elusive because timely engagement in care to allow uninterrupted access to antiretroviral therapy (ART) and sustained viral suppression remain incomplete (1). Our results from a recent study in Zambia, *BetterInfo*, using a sampling-based approach to quantify mortality in the presence of high loss to follow up (LTFU), found that in the contemporary era, mortality among patients starting ART reached 7% at two years – far higher than in developed country settings – and continued to accrue at about 2% per year for up to eight years with LTFU or missing visits as the strongest predictor of mortality (2). The results from the *BetterInfo* study also demonstrated a high prevalence of clinic-based barriers to care, including rude health care worker (HCW) behaviour, short intervals between patient clinic visits, and long wait times at the facility (3). In addition, a similar study conducted in Zambia to understand reasons for patient attrition from HIV care cited amongst others clinic based barriers such as placing defaulters on intensive adherence counselling, thus imposing opportunity costs for patients and long waiting times for medical care. The study further suggested the need to improve patient provider dialogue about patient experiences(3–5). This underscored the need to better understand these clinic-based drivers of engagement and, overall, to improve the patient experience, in essence, a more patient-centred care approach. Unfortunately, little is known about how to evaluate and implement patient-centred care in the public health context of HIV care in sub-Saharan Africa (6). To address these knowledge gaps, we aim to systematically evaluate the overall patient experience and its effect on retention in care and virologic suppression via multiple novel measurement modalities in public ART clinics in Zambia. This study will provide important direction for future interventions to implement more patient-centred care in the current public health HIV infrastructure, as it will fill important knowledge gaps regarding clinic-based barriers to care.

## 2.0 SIGNIFICANCE

Although the evolution of health systems toward decentralization (7) and now differentiated service delivery models (1) have extended the reach of HIV services, gaps remain. In 72 clinics providing treatment to over 180,000 patients in Zambia, the Bill and Melinda Gates Foundation (BMGF)-funded *BetterInfo* study found that 22% of all patients were LTFU after two years (2). Furthermore, the rate of disengagement from care varied by over 10 fold across facilities – differences that were not explained by adjustment for facility size, geographic location nor other characteristics, and which we believe to be due to nature of setting and services at those facilities. Interviews among a random sample of lost patients intensively traced and found in the community revealed variable barriers to care including clinic based barriers (e.g., rude health care workers, excessive facility waiting times) reported by up to 80% of patients by facility, and structural barriers (e.g., transportation, work demands) reported by up to 70% of patients by facility. In addition, we also carried out a discrete choice experiment in which HIV patients were offered a series of choices between two hypothetical facilities with different combinations of attributes and asked which they would prefer – thus quantifying the relative rank and strength of patient preferences – and potentially informing prioritization of health systems improvements. These choice experiments revealed that patients were willing to trade up to 15 hours of waiting time for “kind” health care workers and seven hours of waiting time for longer drug refill intervals. Improving the patient experience and retention represents a critical step toward sustained treatment and full epidemic control.

## 3.0 RATIONALE

Evidence from this study as well as throughout Africa points to the gaps in the patient experience as a crucial area for improvement (3,4,6,8,9). These data offer a simple synthesis and strategy for improvements. That is, when patients perceive encounters with the health system to be high-quality, respectful, accessible, responsive, and effective, engagement is strengthened (9). We therefore set out to make public health HIV treatment more patient centred, manage and enhance perceptions of quality, and strengthen engagement to optimize treatment. To do so,

first, facilities require a scalable measurement platform to systematically capture the patient experience (e.g., satisfaction, perceived quality, communication, patient outcomes) and make this information routinely available to HCWs. Second, a strategy using insights from networking science (interplay of human behaviour, technology and information diffusion) is needed to disseminate perspectives to promote patient centeredness, shared decision making and address prevalent barriers to care. Although a patient centred public health for HIV care in Africa cannot accommodate every individual's circumstances, redesign can better meet the needs of many. Person centred care has been shown to improve outcomes and reduce expenses in medical settings in North America for conditions ranging from diabetes to HIV (8,10–12). Other studies in Zambia and Uganda evaluated the impact of a large health initiative on quality of care and satisfaction among patients and maternal health workers (12). Because the specific barriers to patient engagement vary in intensity and nature across facilities, we believe that measurement of patient-reported experiences at each facilities level represent a crucial strategy for targeting the intensity and nature of improvement efforts. We propose introducing and adapting these practices into the public health setting in Zambia and determining other relevant practices for Zambia to redesign public health delivery.

